**IN interventions**
Number of interventions per patient, duration, location (body region), type, substances used, perceived or reported reactions after the IN intervention, and side effects
**Study participation**
Study inclusion and reasons for noninclusion of patients

#### Data Analysis

Where feasible, complete case analysis will be performed; otherwise, pairwise deletion will be applied. Quantitative data will be analyzed using descriptive statistics, including frequencies, medians, means, and SDs, as appropriate. Subgroup analyses (eg, by sex, age group, diagnosis, or type of IN intervention) will be exploratory in nature. Group comparisons will be conducted using independent samples *t* tests for interval-scaled variables and chi-square tests for categorical variables. If the assumptions for parametric tests are not met, nonparametric alternatives such as the Mann-Whitney *U* test and Fisher exact test will be used. The significance level will be set at 5% (*P*<.05). Qualitative data from the open-ended text fields will be categorized using thematic content analysis.

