## Methods

### Project IMPLEMENT-UKU: Setting and Intervention

The IMPLEMENT-UKU project and its accompanying evaluation study are being carried out as a single-center initiative at the University Hospital Ulm. Within the framework of the project, patients with cancer on participating wards receive IN interventions as supportive care during their hospital stay as part of a consultation service. Figure 1 illustrates a flowchart of the patient care pathway within the project.

Patients will be referred to an initial IN consultation by nursing or medical staff on the participating wards. Referrals will be based on pertinent and acutely distressing symptoms and problems, such as restlessness, pain, or cancer-related side effects, which are relevant to care and indicate the need for supportive interventions. Following referral, patients will receive an initial IN consultation, which may be followed by additional IN visits and interventions throughout their hospital stay. During the initial IN consultation, the integrative nurse will provide information about IN, the overarching IMPLEMENT-UKU project, and the ongoing evaluation study. The first IN intervention will be conducted directly after this consultation. The number of subsequent IN visits and interventions may vary depending on patient needs and the duration of hospitalization.

Depending on each patient’s symptom burden and individual preferences, patient-tailored IN interventions will be offered alongside routine care. To ensure consistent application, these interventions will be guided by a symptom-driven IN intervention catalog (Table 1). The IN catalog was developed through an expert consensus process, drawing on external naturopathic nursing textbooks [11,12,44-47], academic literature [14,15,18,19,48], and recommendations from previous projects and guidelines [36,49-51]. To ensure intervention fidelity, standard operating procedures are available for all IN interventions.

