#### Data Collection

Project-related routine documentation will serve as the data source for all IN consultation requests, as well as the corresponding IN visits and interventions. Data for participants in substudy 1 will be collected pseudonymously, while data for all other project participants will be extracted anonymously.

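### Substudy 5 names independent-samples tests, including for comparisons by intervention type, although visits and interventions repeat within patients; P values from row-by-row comparisons would be invalid

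*Protocol article*

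**What the plan says.** The Data Analysis section of Substudy 5 puts description first and then names tests: "Group comparisons will be conducted using independent samples" t "tests for interval-scaled variables and chi-square tests for categorical variables". Where parametric assumptions fail, it offers "nonparametric alternatives such as the Mann-Whitney" U test and the Fisher exact test. The threshold is P<.05. On grouping factors it says "Subgroup analyses (eg, by sex, age group, diagnosis, or type of IN intervention) will be exploratory in nature".

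The data are described elsewhere in the article:

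- Textbox 1 lists, for interventions, "Number of interventions per patient, duration, location (body region), type, substances used, perceived or reported reactions after the IN intervention, and side effects". The number of interventions is one value per patient. Duration, type, reactions and side effects belong to the single intervention. The visit entry mixes units in the same way.
- The setting section says "The number of subsequent IN visits and interventions may vary depending on patient needs and the duration of hospitalization". The Discussion overview expects repeated visits and interventions for each patient.
- The Introduction names compresses, embrocations, baths and washes as kinds of IN intervention. Table 1 offers several of these for one symptom; sleep disorders, for example, list compresses, baths and embrocations.
- Under Data Collection, records of Substudy 1 participants are pseudonymous, while "data for all other project participants will be extracted anonymously".

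The section does not state the unit of analysis. It names no method for repeated records, and none for an interval outcome across three or more groups.

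**The concern.** All four named tests assume that observations are independent. Several records from one patient are not: the same person, symptoms and preferences lie behind each of them. Type of intervention raises a further difficulty, because one patient can appear in several of the groups being compared. Averaging to one value per patient and type would still not make those groups independent samples.

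These comparisons have a purpose in the article. The setting section promises to examine how delivery varies with patient characteristics. Fidelity is defined through features of the single intervention, such as its duration. The Limitations section relies on documented variability to offset incomplete standardization, and the mixed methods section lists subgroup effects among the possible explanations for discrepant findings. A P value from the wrong error model could create an apparent pattern or hide a real one.

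**Working it through.** **Inputs**

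- Nominal level: 5%, from Substudy 5 Data Analysis. Sidedness is not stated; two-sided is assumed.
- Records per patient (m) and ICC: neither is given. The assumed ranges are m = 2 to 5 and ICC = 0.1 to 0.5.
- Patients, used only to size the simulations: about 20 eligible per month (Substudy 1, Participants) × 16 calendar months (October 2023 to January 2025, counted inclusively) = 320. Substudy 5 covers all requests and all project patients, so the 30% recruitment rate of Substudy 1 is not applied.

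**Step 1. Reproduce the stated level.** With one value per patient and two groups, the level is 2 × [1 − Φ(1.96)] = 5.0%. Simulated t tests (320 patients, 4,000 runs) reject in 4.5% to 5.6% of runs on patient means and in 4.3% with one record per patient. A 5 × 2 chi-square test on patients rejects in 4.6%. The simulation standard error is √(0.05 × 0.95 / 4,000) ≈ 0.34 percentage points, so all of these agree with 5% to within about two standard errors.

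**Step 2. Record-level outcome, patient-level factor (sex, age group, diagnosis).** The variance is inflated by DEFF = 1 + (m − 1) × ICC, and the actual level is 2 × [1 − Φ(1.96 / √DEFF)].

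| m | ICC 0.1 | ICC 0.3 | ICC 0.5 |
|---|---|---|---|
| 2 | DEFF 1.1: 6.2% | 1.3: 8.6% | 1.5: 11.0% |
| 3 | 1.2: 7.4% | 1.6: 12.1% | 2.0: 16.6% |
| 5 | 1.4: 9.8% | 2.2: 18.6% | 3.0: 25.8% |

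At m = 4 the formula gives 15.5% (ICC 0.3, DEFF 1.9) and 21.5% (ICC 0.5, DEFF 2.5). Simulated t tests give 15.7% and 21.7%, and 9.4% at m = 2 with ICC 0.3.

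The table assumes equal numbers of records. If the numbers vary, as the setting section says they may, DEFF = 1 + (mean + variance/mean − 1) × ICC. With mean 4 and variance 3 this is 1 + 3.75 × ICC, or 2.125 and 2.875 at ICC 0.3 and 0.5. The levels are then about 18% and 25%, so unequal numbers make the error worse.

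**Step 3. Record-level outcome, intervention type.** Simulated with two types, 2 to 4 records per patient and ICC 0.3 to 0.5:

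- Type falls at random over records: 5.2% to 5.5%.
- Every patient has the types in equal numbers: 0.5% to 1.9% (conservative).
- Patients mostly receive one type (90/10): 7.1% to 15.9%.

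**Step 4. More than two groups.** The t and Mann-Whitney tests compare two groups. Four classes of intervention form 4 × 3 / 2 = 6 pairs. One overall test keeps 5%. Six unadjusted pairwise tests would give 20.2% (simulated, allowing for correlated contrasts), or 1 − 0.95⁶ = 26.5% if treated as independent. The article does not plan such testing, so these figures show only why an overall test should be named.

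**The case against.** A reader might infer that all Substudy 5 P values will be wrong. The article does not support that. It never says that visit or intervention rows will be treated as independent. Numbers of visits, numbers of interventions and study inclusion are one value per patient, and there the named tests keep about 5% between two groups. Acceptance of the offer does so too if each patient is counted once.

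Nor are all the named tests limited to two groups. Chi-square, and Fisher exact in its larger-table form, take more. The nonparametric list is open-ended. Only intervention type can be shown from the article to have more than two classes; the levels of age group and diagnosis are not given.

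A reader might also infer that anonymous extraction has already broken the link between one patient's records. The article does not say so, and counts per patient imply some grouping at source. It only mentions no key, which is a reason to check.

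The strongest argument is one of weight: the subgroup analyses are labelled exploratory, Substudy 5 is mainly descriptive, and an article may leave the unit of analysis to a fuller plan. That lowers the severity, and silence on the unit is not in itself the fault. It does not remove the point. The article does name the tests and does name intervention type as a factor, and the two do not fit. The exploratory label excuses low power and the lack of multiplicity control, but not a P value computed under a false independence assumption.

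**Conclusion.** The point holds for visit- and intervention-level variables and for comparisons by intervention type. Applied row by row, the named tests would not have the stated 5% level. For patient-level factors the actual level is about 6% to 26% under the assumed 2 to 5 records per patient and ICC 0.1 to 0.5. The low end is a minor error and the high end a serious one, and the article gives no figures to say where the study lies. For intervention type the direction depends on how types are spread over patients, from strongly conservative to clearly inflated. Two-group comparisons of one-value-per-patient outcomes stand as planned. Severity is moderate.

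**What to change.** State the unit of analysis for each Substudy 5 outcome, then:

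- For visit- and intervention-level variables, use a linear or logistic mixed model, or GEE with robust standard errors, with patient as the cluster. For patient-level factors, a patient-level summary with a simple test is an acceptable alternative.
- For interval outcomes over more than two groups, use one overall test: a joint test of the factor in the clustered model, or ANOVA or Kruskal-Wallis where there is one value per patient.
- Keep the t, Mann-Whitney, chi-square and Fisher tests for one-value-per-patient variables.
- Confirm that the anonymous extract carries a non-identifying within-patient key. Where it does not, report record-level comparisons descriptively, without P values.

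The cost is a revised analysis paragraph, somewhat more analysis work and some less favourable P values. The article reports data collection complete in March 2025 and analysis still under way in October 2025. At that stage the methods could still be changed, but a missing key might not be recoverable, so that check comes first.

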### Mixed Methods Analysis

After the separate analysis of each sub-study, the results will be integrated to generate meta-inferences. The ensuing discussion will examine areas of convergence, divergence, complementarity, and the relationships between the quantitative and qualitative findings, as well as different perspectives on the implementation of IN. The interpretation will be grounded in comparisons and correlations [52,64].

Triangulation approaches will be used to compare and integrate data, enabling both cross-validation and enrichment of the findings [65]. Methodological triangulation will enhance the credibility of results by identifying consistencies and discrepancies across different types of data, such as comparing quantitative and qualitative findings on patients’ perspectives regarding the implementation of IN. Data source triangulation will be applied by incorporating insights from patients, relatives, and health care professionals, enabling a more comprehensive understanding of the implementation of IN for inpatients.

Integrative data analysis will use joint displays to present and synthesize findings, enabling further conclusions [66,67]. A joint display is a matrix that visually aligns and compares results from different data types to support systematic integration. In this study, which follows a convergent design, a side-by-side comparison will be used [67]. Joint displays will be thematically structured, such as according to the domains of to CFIR [57]. These displays will support the development of new insights and conclusions that extend beyond the individual substudies, serving as a foundation for interpretation, discussion, and stakeholder dialogue.

During the integration process, discrepancies between qualitative and quantitative findings will be systematically examined. Rather than being regarded as limitations, these divergences will be considered opportunities for deeper interpretation. They will be mapped in joint displays and explored through iterative team discussions to generate plausible explanations, including contextual factors or subgroup effects. This process will be transparently documented to ensure rigor.

### Ethical Considerations

The evaluation study was conducted in accordance with the Declaration of Helsinki and received ethical approval from the Ethics Committee of the University of Ulm, Germany (144/23). All participants will receive detailed verbal and written information about the project and study objectives as part of the informed consent process. Informed consent will be obtained before participation, ensuring that participation is entirely voluntary. Participants may withdraw from the study at any time without providing a reason and without facing any consequences.

## Results

Initially, the results of each substudy will be analyzed independently. Thereafter, the findings will be integrated and triangulated across the substudies, incorporating both quantitative and qualitative data, as well as the perspectives from different stakeholders, to develop comprehensive meta-inferences. The recruitment phase lasted from October 2023 to January 2025. Data collection was completed in March 2025. As of October 2025, after data verification and plausibility checks, data analysis is ongoing. The first results are expected to be published in 2026.

## Discussion

### Overview

This study outlines the protocol for mixed methods research aimed at making a theory-based contribution to the implementation of IN for inpatients and examining its potential effects at the patient level. The following anticipated findings are derived from the study’s research questions: IN visits and interventions are expected to be implemented as intended, with a moderate to high number of IN consultation requests and repeated IN visits and interventions per patient during the hospital stay. Acceptance rates among patients and staff are likely to be high, with health care professionals perceiving IN as a meaningful complement to conventional care. Contextual, structural, and organizational factors are anticipated to act as key barriers and facilitators in the implementation process. Initial results are expected to show improvements in well-being, reductions in symptom burden, and increased self-efficacy. IN interventions are anticipated to be perceived as supportive and not associated with additional burden. Patients may also report short-term subjective benefits such as enhanced vitality, a sense of warmth and strength, and feelings of calm following IN interventions.

The findings can subsequently be compared and contextualized with studies that have implemented CIM or IN in other settings, such as pediatric care [37,38,40,41,68-70] and outpatient oncology care [35,42,71,72], as well as with studies and programs offering IO for patients [33,73-75]. Situating the findings within the framework of implementation science is essential for advancing both the conceptual development and practical integration of IN into routine care [76]. This research is expected to make a substantial contribution to the implementation of IN as a service for inpatients. Furthermore, the findings will support the German Research Agenda for Nursing Oncology and help establish a scientific foundation for IN in oncology care [43].

The findings of this study will first be shared with the interdisciplinary IMPLEMENT-UKU Steering Committee. The results are expected to be suitable for publication in peer-reviewed journals and for presentation at national and international conferences. As part of the dissemination strategy, the results of the individual substudies will be published separately, followed by an integrative mixed methods publication synthesizing the overall findings. In addition, the results will be shared with the general public through patient forums, information events, and the project website. The findings will also inform the ongoing development and improvement of the IMPLEMENT-UKU project’s implementation strategy. The findings may contribute to the development of practical guidelines to support the standardization and facilitation of IN implementation in other hospital settings. Moreover, the study outcomes are expected to inform future research strategies in the fields of IN and implementation science.

### Limitations

The monocentric design of this study may limit the generalizability of findings to other settings and reduce external validity, as the results reflect the specific implementation context at Ulm University Hospital. Furthermore, due to the patient-centered and multimodal nature of the IMPLEMENT-UKU project, the delivery of IN interventions is not fully standardized and may vary between patients. To ensure consistency, all IN interventions are guided by a symptom-driven IN catalog, which supports targeted and structured application. In addition, a standard operating procedure is in place, and all applied IN interventions are documented in detail through project-specific documentation, enabling analysis of IN intervention variability and its impact.

As participation in this study is voluntary, there is potential for recruitment bias and corresponding selection bias. Although a convenience sampling approach will be used, several strategies will mitigate these limitations. Recruitment and sampling procedures will be transparently documented, and reflexivity will be maintained throughout the recruitment and data analysis phases. Reasons for exclusion and refusal to participate will be systematically recorded. For the qualitative interviews, efforts will be made to ensure heterogeneity in key participant characteristics.

As the studies rely primarily on self-report measures, risk of response bias, recall bias, and social desirability bias must be considered. In substudy 3, the cross-sectional design and convenience sampling of relatives from a single hospital limit external validity and generalizability. Substudy 1 uses a pre-post design without a control group. While this design enables the observation of intra-individual changes over time, it does not permit causal inference, as observed effects cannot be attributed solely to the intervention, thereby limiting internal validity. Accordingly, only exploratory analyses are planned to generate preliminary insights into potential effects and inform future research directions. Nevertheless, triangulation across multiple data sources within the patient group will enhance the credibility and trustworthiness of the findings, despite the nonprobabilistic sampling.

## Abbreviations

CFIR: Consolidated Framework for Implementation Research
CIM: complementary and integrative medicine
IMPLEMENT-UKU: Implementation of Integrative Nursing at the Ulm University Hospital
IN: integrative nursing
IO: integrative oncology
